## Abstract

•Protocol for external validation of Pre-ECPR score for patient selection in ECPR.•In development, the score achieved AUC 0.79 vs 0.63 for ELSO selection criteria.•Prague OHCA-trial provides an ideal external validation cohort: 92 ECPR patients.•Prospective data with all physiological predictors systematically collected.•We present a pre-specified validation framework with blinded outcome assessment.

Protocol for external validation of Pre-ECPR score for patient selection in ECPR.

In development, the score achieved AUC 0.79 vs 0.63 for ELSO selection criteria.

Prague OHCA-trial provides an ideal external validation cohort: 92 ECPR patients.

Prospective data with all physiological predictors systematically collected.

We present a pre-specified validation framework with blinded outcome assessment.

## Introduction

Cardiac arrest remains a major public health challenge, and despite optimization of conventional cardiopulmonary resuscitation (CPR), many patients fail to achieve return of spontaneous circulation.^1^ Extracorporeal CPR (ECPR) has emerged as a promising intervention for selected patients with refractory cardiac arrest, and American Heart Association guidelines state that the use of ECPR for patients with cardiac arrest refractory to standard advanced cardiac life support (ACLS) is reasonable in selected patients when provided within an appropriately trained and equipped system of care (moderate recommendation with moderate-quality evidence).^2^ Meta-analyses suggest that approximately 20 % of patients treated with ECPR achieve favorable neurological outcomes, defined as a modified Rankin Scale (mRS) of 0–3.^3^, ^4^, ^5^ Consequently, a majority (80 %) of ECPR-patients experience poor outcomes, which is particularly problematic given ECPR's resource-intensive nature.^6^ Optimal selection criteria could minimize futile care while preserving access for those most likely to benefit.^4^

Current selection strategies demonstrate significant heterogeneity, with a systematic review identifying 93 different ECPR selection protocols in the literature.^6^ These protocols typically incorporate age, no-flow time, and low-flow time, and some incorporate physiological parameters such as end-tidal CO_2_ levels or signs of life during CPR.^6^, ^7^, ^8^ The continuous variables are generally converted into binary inclusion or exclusion criteria, with cut-off thresholds varying substantially between protocols.^6^ This dichotomization of continuous parameters represents a major limitation, transforming continuous variables into yes/no criteria with artificial thresholds that fail to capture dynamic relationships with outcomes. Recent retrospective studies demonstrate that restrictive criteria increase survival rates among selected patients but exclude actual survivors who did not fulfill all criteria.^8^, ^9^, ^10^ Liberal criteria, in contrast, exclude few patients, but result in high rates of futile care and low survival rates. Furthermore, evaluation of the patient during ongoing arrest remains limited in most protocols.^4^, ^5^, ^6^ While registry-based prognostic models have been developed, they are limited by available predictors and lack clear ECPR-decision thresholds.^11^, ^12^ As noted in the Extracorporeal Life Support Organization (ELSO) guidelines: “robust data to identify those who may benefit from ECPR are lacking”.^13^

To address these limitations, the Pre-ECPR score was developed using logistic regression to incorporate multiple weighted predictors as continuous variables, predicting the probability of favorable neurological outcomes at one year.^10^ The model incorporates standard predictors and a comprehensive evaluation of circulatory and neurological status during active resuscitation. In internal cross-validation, the score demonstrated superior discriminative performance compared to the ELSO example of selection criteria for ECPR (area under the receiver operating characteristic curve [ROC AUC] 0.79 vs. 0.63, *P* = 0.012).^10^, ^13^ A threshold yielding 100 % sensitivity and 44 % specificity for favorable outcomes was identified. However, external validation is essential to assess the score's generalization performance and reproducibility across different healthcare settings.^14^ The Prague Out-of-Hospital Cardiac Arrest (OHCA) trial provides a well-suited cohort for this purpose, comprising 92 ECPR-treated patients in a prospective randomized clinical trial with systematic collection of pre-ECPR variables and standardized neurological outcome assessments.^15^

This protocol paper outlines the planned methodology for external validation of the Pre-ECPR score, following the framework for external validation by Debray et al.^14^ and adhering to the Transparent Reporting of a multivariable prediction model for Individual Prognosis Or Diagnosis prediction model + AI (TRIPOD + AI) guidelines.^16^ We describe our approach to evaluating the model's predictive performance and validating previously identified decision-making thresholds through blinded probability calculations and cohort comparisons, thereby establishing a methodological foundation before conducting the validation analysis.

## Methods

Ethical approval was obtained from the Regional Ethics Committee of Gothenburg and the Swedish Ethical Review Authority (Dnr 288-17 and 2025-00620-02) and the institutional review board of the General University Hospital and First Faculty of Medicine, Charles University in Prague (192/11S-IV). The study was registered at ClinicalTrials.gov (NCT04198792).

### Validation cohort

The validation cohort consists of 92 ECPR patients from the Prague OHCA trial, a single-center randomized controlled trial conducted in Prague between March 2013 and October 2020.^15^ The cohort includes adults aged above 18 years who received ongoing resuscitation for witnessed refractory OHCA of presumed cardiac etiology, with inclusion and exclusion criteria detailed in Table 1. Patients were randomized to either invasive strategy (immediate transport for ECPR) or standard strategy (continued on-site CPR). Some patients initially randomized to the standard strategy subsequently crossed over to receive ECPR and are included in this validation cohort, flow diagram in Fig. 1.

**Table 1 t0005:** Inclusion and exclusion criteria for the validation cohort, adapted from the Prague OHCA trial.

**Inclusion criteria**	**Exclusion criteria**
**Entry criteria for enrollment into the Prague OHCA trial**	
Age ≥18 and ≤65 years^a^	OHCA of presumed non-cardiac cause
Witnessed OHCA of presumed cardiac cause	Unwitnessed collapse
Minimum of 5 min of ACLS performed by the EMS team without sustained ROSC	Suspected or confirmed pregnancy
Unconsciousness^b^	ROSC within 5 min of ACLS performed by EMS team
ECLS team and ICU bed capacity in cardiac center available	Conscious patient
	Known bleeding diathesis or suspected/confirmed acute or recent intracranial bleeding
	Suspected or confirmed acute stroke
	Known severe chronic organ dysfunction or other limitations in therapy
	“Do not resuscitate” order or other circumstances making 180-day survival unlikely
	Known pre-arrest cerebral performance category (CPC) ≥ 3

**Criteria for initiation of ECLS in the invasive strategy group of the Prague OHCA trial**	
No return of spontaneous circulation or return of spontaneous circulation with ongoing shock (defined as sustained hypotension below 90 mmHg of systolic pressure or need for moderate to high doses of vasopressors)	Signs of death or irreversible organ damage
Admission to cathlab not later than 60 min after the collapse/initial call to emergency medical service^c^	Known bleeding diathesis
Consensus of cardiac center team members on extracorporeal life support initiation	Inadequate arterial and/or venous access for femoro-femoral cannulation

Abbreviations: ACLS: advanced cardiac life support; CPC, cerebral performance category; ECLS, extracorporeal life support; EMS, emergency medical services; ICU, intensive care unit; OHCA, out-of hospital cardiac arrest; ROSC, return of spontaneous circulation.

a Age was estimated at the scene of cardiac arrest; patients later found to be older than 65 years were retained in the study.

b Defined as no response to verbal or painful stimuli during ACLS.

c If collapse time was not exactly known, initial call to emergency medical service was considered.

**Fig. 1 f0005:**
[figure not shown]
**Flow diagram of the external validation of the Pre-ECPR score using data from the Prague OHCA trial**. A total of 92 ECMO patients will be included in the validation cohort: 82 from the ECPR arm and 10 who crossed over from the standard CPR arm. Patients will be stratified by neurological outcome at one year (favorable: mRS 0–3; unfavorable: mRS 4–6) and by Pre-ECPR score above or below various threshold levels, including the previously identified 6.4% probability cut-off. CPR, cardiopulmonary resuscitation; ECMO, extracorporeal membrane oxygenation; ECPR, extracorporeal cardiopulmonary resuscitation; mRS, modified Rankin Scale; OHCA, out-of-hospital cardiac arrest.

Patients in the invasive strategy group received mechanical chest compression (LUCAS, Lund University Cardiac Arrest System; Physio-Control Inc/Jolife AB, Lund, Sweden) initiated on scene and were immediately transported to the cardiac catheterization laboratory during ongoing CPR. Drug administration, defibrillations, and other interventions during transport followed European Resuscitation Council guidelines.^17^, ^18^ Intra-arrest intranasal evaporative cooling via a RhinoChill (BeneChill Inc, San Diego, California, USA) device was used when feasible until its discontinuation in 2016.

Patients in the standard strategy group received continued advanced cardiac life support on site according to European Resuscitation Council guidelines. Mechanical chest compression device use was at physician discretion. Ten patients in this group subsequently received ECPR after crossover to the invasive strategy.

Extra corporeal membrane oxygenation (ECMO) cannulation was performed at the catheterization laboratory during ongoing mechanical CPR using a femoro-femoral approach. Following ECMO initiation, patients underwent diagnostic and therapeutic procedures including coronary angiography and percutaneous coronary intervention when indicated. An antegrade perfusion cannula was implanted in the cannulated limb under ultrasound guidance. Continuous anticoagulation with heparin was administered targeting an activated partial thromboplastin time of 50–70 s. All patients underwent immediate biochemical evaluation, urgent bedside echocardiography, and whole-body computed tomography when clinically indicated. Target temperature management to 33 °C was initiated using either the ECMO heat exchanger or other cooling devices. Following publication of updated trial results, temperature management to 36 °C was permitted in cases with early awakening or hypothermia-related complications.^19^ All other post-arrest critical care management, including withdrawal of life-sustaining therapy decisions, followed European Resuscitation Council guidelines.^17^, ^18^

### Outcome

The primary endpoint of the validation is 1-year survival with favorable neurological outcomes, defined as mRS 0–3, consistent with the definition used in Pre-ECPR score development.

In the validation cohort, a neurologist blinded to the initial treatment strategy assessed neurological outcomes at two timepoints: at 6 months after ECPR treatment using the cerebral performance category (CPC) scale, and at a median of 5.3 (interquartile range 3.8–7.2) years using both CPC and mRS scales. To determine 1-year mRS scores, medical records will be systematically reviewed for any intervening events that may have altered neurological status.

### Blinding

The probability of a favorable outcome will be calculated for each individual in the validation cohort while blinded to outcome data. Similarly, comparisons between the model development cohort and validation cohort will be performed blinded to the outcome. Thereafter, outcomes will be unblinded to enable full model performance evaluation and subsequent analyses.

### Prediction model

The Pre-ECPR score estimates the probability of favorable neurological outcomes, defined as an mRS score of 0–3, one year after ECPR.^10^ The model incorporates eight prognostic factors, with five of these being measurements or evaluations performed during the arrest (Fig. 2). The Pre-ECPR score is calculated using a logistic regression model, in which each factor is weighted by its corresponding regression coefficient and contributes to the overall predicted probability of favorable neurological outcomes. Factors include age and total cardiac arrest time (defined as the interval from cardiac arrest onset to ECMO flow initiation). The no-flow time, initial rhythm, and first CPR provider are merged into one variable (no-flow/initial rhythm) with three categories. The first category, “ACLS by medical providers immediately at the cardiac arrest”, refers to situations when medical providers are present at the time of cardiac arrest and initiate ACLS at the moment of the arrest. The two “no immediate ACLS” categories refer to situations in which no ACLS team is present at the time of cardiac arrest. Bystander CPR may have been provided, but the initial rhythm detected later by the ACLS team reflects the degree of anoxic injury sustained by the heart, brain, and body during the no-flow period. These categories are: “No immediate ACLS and first detected rhythm ventricular fibrillation or tachycardia (VT/VF)” and “No immediate ACLS and first detected rhythm pulseless electrical activity (PEA)/asystole”. The former typically indicates less anoxic injury than the latter. Variables assessed at the time of ECMO decision include pupil size, end-tidal CO_2_, signs of life, regional cerebral oxygen saturation (rSO_2_) measured using INVOS 5100 (Medtronic, Minneapolis, MN, USA), and arterial pH closest to the time of ECMO initiation. Signs of life, defined as spontaneous movements or breathing efforts, are categorized into three levels: (a) present, (b) absent, or (c) unable to assess due to sedation or muscle relaxant administration. Measurements of cerebral rSO_2_ are not transferable between brands in cardiac arrest patients; therefore, only INVOS-measured rSO_2_ can be used in the score.^20^ A modified version of the score, excluding INVOS rSO_2_ or arterial pH when missing, is also available; see Table 2 for corresponding formulas. The score is applicable to both in-hospital cardiac arrests (IHCA) and OHCA patients. A Pre-ECPR score calculator is available at ecprscore.org.

**Fig. 2 f0010:**
[figure not shown]
**Assessment points of the Pre-ECPR score**. *Asterisks indicate the eight predictors of the Pre-ECPR score. The composite no-flow/initial-rhythm variable with three levels is determined at cardiac-arrest onset. During CPR, at the time of the ECMO decision, age and patient status are assessed. Signs of life (spontaneous movements or breathing) are classified as present, absent, or unable to assess due to sedation or muscle-relaxant administration. In addition, pupil size, end-tidal CO_2_, INVOS rSO_2_, and arterial pH are assessed. ACLS, advanced cardiac life support; CPR, cardiopulmonary resuscitation; ECMO, extracorporeal membrane oxygenation; INVOS rSO_2_, regional cerebral oxygen saturation measured by near-infrared spectroscopy; PEA, pulseless electrical activity; VF, ventricular fibrillation; VT, ventricular tachycardia.

**Table 2 t0010:** Model specification and regression coefficients for full and modified Pre-ECPR scores.

**Variables**	**Full Pre-ECPR score** **ß coefficient**	**Pre-ECPR score** **without arterial pH** **ß coefficient**	**Pre-ECPR score** **without INVOS rSO**_**2**_ **ß coefficient**
Intercept	**–9.791**	**–6.404**	**–8.827**
Ln (85 – age) [years]	1.593	1.360	1.543
**No-flow time/first rhythm**			
Direct ACLS at CA	0.000	0.000	0.000
No direct ACLS, first rhythm VT/VF	–0.505	–0.514	–0.278
No direct ACLS, first rhythm PEA/asystole	–4.000	–4.000	–4.000
Ln (CA-time) [min]	–0.304	–0.334	–0.324
**Signs of life**			
Not moving or breathing	0.000	0.000	0.000
Not moving or breathing, but sedation or muscle relaxant administered	0.772	0.782	0.798
Moving or breathing	1.528	1.304	1.449
Pupils ≥ 6 mm	–3.916	–3.840	−3.880
Ln (End-tidal CO_2_) [kPa]	0.471	0.693	0.640
Ln (INVOS rSO_2_-14)	0.505	0.513	NA
Ln (Arterial pH-5)	3.799	NA	3.980

Prediction formula (full model): *P*(favorable outcome) = 1/(1 + exp(−LP)), where LP = −9.791 + 1.593 × ln(85-age) − 0.505 if VT/VF − 4.000 if PEA/asystole − 0.304 × ln(CA-time) + 0.772 if sedation given + 1.528 if moving/breathing – 3.916 if pupils ≥ 6 mm + 0.471 × ln(ETCO_2_) + 0.505 × ln(rSO_2_-14) + 3.799 × ln(pH-5). Model constraints: age ≤ 85 years; ETCO_2_ ≥ 1 kPa; rSO_2_ ≥ 15 % (device minimum); pH ≥ 6.

The Pre-ECPR score calculator is available at ecprscore.org.

Abbreviations: ACLS, advanced cardiac life support; CA, cardiac arrest; ECPR, extracorporeal cardiopulmonary resuscitation; ETCO_2_, End-tidal CO_2_; NA, not applicable; PEA, pulseless electrical activity; rSO_2_, regional cerebral oxygen saturation; VT/VF, ventricular tachycardia or ventricular fibrillation.

In the original publication, the Pre-ECPR score demonstrated an ROC AUC of 0.79 (95 % confidence interval [CI] 0.67–0.88) in five-fold internal cross-validation.^10^ No patients with predicted probabilities below 6.4 % achieved favorable outcomes. Above this threshold, the score demonstrated a specificity of 44 % and a positive predictive value of 40.5 % for favorable outcomes. The probability thresholds for 97 % and 94 % sensitivities of favorable outcomes were 12.6 % and 16.0 %, respectively.

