If the original model demonstrates suboptimal performance or a significant lack of fit in the validation cohort, recalibration will be performed by updating the model intercept and/or calibration slope to align predicted probabilities with observed outcomes. If miscalibration persists or there is evidence of poor discrimination, model refitting may be undertaken, involving re-estimation of model coefficients using the validation data. The performance of the recalibrated or refitted model will then be evaluated through internal cross-validation within the validation cohort to assess the stability and generalizability of calibration estimates.

The Pre-ECPR score is based on a multivariable logistic regression model incorporating eight predictors. To calculate the individual Pre-ECPR score probabilities in the validation cohort, the full model will be used when all data are present, Table 2. Alternative model equations for cases in which arterial pH or INVOS rSO_2_ is missing are available, and for other missing-data patterns further model equations (2*^k^* submodels) will be derived in the development cohort.^22^ Multiple imputation will be used to compute the c-statistics for cohort membership.

Statistical analyses will be conducted using R software (version 4.4.3 or later; R Foundation for Statistical Computing, Vienna, Austria), and results will be reported in accordance with the TRIPOD + AI guidelines.^16^

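### The full-model formula printed under Table 2 drops conditions that the Table 2 rows carry, so coding it as printed gives different probabilities for three identifiable patient groups

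*Protocol article*

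**What the plan says.** Table 2 of the protocol article specifies the Pre-ECPR score. Two of its predictors have three mutually exclusive levels.

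- **No-flow time/first rhythm.** "Direct ACLS at CA" scores 0.000 with no rhythm condition. "No direct ACLS, first rhythm VT/VF" scores -0.505 in the full model, and "No direct ACLS, first rhythm PEA/asystole" scores -4.000. The Prediction model section agrees: the first category "refers to situations when medical providers are present at the time of cardiac arrest and initiate ACLS at the moment of the arrest", and rhythm separates only the two categories without immediate ACLS.
- **Signs of life.** Not moving or breathing scores 0.000, "Not moving or breathing, but sedation or muscle relaxant administered" scores 0.772, and moving or breathing scores 1.528.

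The note under the table writes out the full model as one formula. There the rhythm penalties depend on rhythm alone, for example "4.000 if PEA/asystole", and the signs-of-life terms read "0.772 if sedation given + 1.528 if moving/breathing". Direct ACLS does not appear in the formula.

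For the blinded calculation, the Statistical analysis section says that "the full model will be used when all data are present, Table 2". It does not say whether the rows or the formula beneath them govern.

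**The concern.** The formula is the only complete computing instruction in the article, and it disagrees with the table it summarises. It leaves out the no-direct-ACLS condition on both rhythm terms and the not-moving-or-breathing condition on the sedation term. It also shortens sedation or muscle relaxant to sedation alone.

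The validation rests on probabilities calculated once, before outcomes are unblinded (Blinding section). If someone codes the formula as printed, some patients receive a probability from a model other than the one developed, and that difference would be read as a failure of the score. The 6.4% cut-off is the most exposed result, because its reported property is that no patient below it had a favorable outcome. With 20 events (Sample size section), one patient with a favorable outcome wrongly placed below the cut-off would lower sensitivity by 1/20, or 5 percentage points. Other groups may also code the score from this article.

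**Working it through.** **Inputs.** The coefficients are those of the full-model column of Table 2, with P = 1/(1 + exp(-LP)). The cut-off is 6.4% (text after Table 2). The article gives no worked patient to reproduce.

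**Check of the coefficients.** Every coefficient in the formula equals the full-model column. Only the conditions attached to four category terms differ.

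**Shift in the linear predictor, formula minus Table 2 rows**

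| Patient group | Table 2 rows | Formula as printed | Shift | Effect on odds |
|---|---|---|---|---|
| Direct ACLS, PEA/asystole | 0.000 | -4.000 | -4.000 | divided by exp(4.000) = 54.6 |
| Direct ACLS, VT/VF | 0.000 | -0.505 | -0.505 | divided by exp(0.505) = 1.66 |
| Sedated but moving or breathing | 1.528 | 0.772 + 1.528 = 2.300 | +0.772 | times exp(0.772) = 2.16 |

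These shifts do not depend on the other predictors. For patients without direct ACLS who are sedated and not moving, or who are unsedated, the two readings agree.

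**Effect at the cut-off.** logit(0.064) = ln(0.064/0.936) = -2.683.

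- Direct ACLS with PEA/asystole: -2.683 + 4.000 = 1.317, which is P = 78.9%. Every such patient with a Table 2 probability from 6.4% to 78.9% falls below the cut-off under the formula. If the patient is also sedated and moving, the two errors partly offset and the net shift is -3.228.
- Direct ACLS with VT/VF: -2.683 + 0.505 = -2.178, which is P = 10.2%. Patients from 6.4% to 10.2% fall below.
- Sedated but moving, no direct ACLS: -2.683 - 0.772 = -3.455, which is P = 3.1%. Patients from 3.1% to 6.4% rise above.

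**Illustration.** The profile is assumed, not taken from the article: age 55, arrest time 60 min, ETCO2 4 kPa, rSO2 40%, pH 7.00, pupils under 6 mm.

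Base LP = -9.791 + 1.593 ln(30) - 0.304 ln(60) + 0.471 ln(4) + 0.505 ln(26) + 3.799 ln(2.00)
= -9.791 + 5.418 - 1.245 + 0.653 + 1.645 + 2.633 = -0.686 (summed before rounding).

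- Direct ACLS, PEA, not moving, unsedated: rows LP -0.686, P = 33.5%; formula LP -4.686, P = 0.9%.
- Direct ACLS, VT/VF, not moving, unsedated: rows 33.5%; formula LP -1.191, P = 23.3%.
- No direct ACLS, VT/VF, sedated but moving: rows LP -1.191 + 1.528 = 0.337, P = 58.3%; formula LP -1.191 + 2.300 = 1.109, P = 75.2%.

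**Range.** The probabilities depend on the assumed inputs. At a less favorable profile (age 65, 75 min, ETCO2 2 kPa, rSO2 25%, pH 6.80) the three comparisons are 7.2% against 0.1%, 7.2% against 4.5%, and 17.7% against 31.7%. At a more favorable one (age 30, 45 min, ETCO2 5 kPa, rSO2 60%, pH 7.20) they are 75.4% against 5.3%, 75.4% against 65.0%, and 89.5% against 94.9%.

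**Age limit.** The stated constraint allows age 85, where ln(85 - age) = ln(0) is undefined. The limits given for ETCO2, rSO2 and pH keep their logarithms defined.

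**The case against.** The best defence is that the formula is shorthand. It sits under rows that state the conditions in full, and the Prediction model section and the Fig. 2 caption repeat both three-level variables. The two reduced models have no written-out formula and can be coded only from the rows. The investigators will derive further submodels in the development cohort, so they hold the variable coding, and an online calculator exists. All of this stands. It makes the intended model clear to a careful reader and a coding error by the study team less likely. It does not make the printed formula correct, because the formula still gives a different answer from its own table.

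A reader might infer that the validation will be distorted, or that the score's coefficients are wrong. The article supports neither. The coefficients agree throughout. The article does not report how many of the 92 patients had direct ACLS, or were sedated yet moving, and either number could be zero. Witnessed arrest is an entry criterion and arrests witnessed by the emergency team are not listed as excluded, so direct-ACLS patients may be present, but no more can be said. An arrest witnessed by that team also counts as direct ACLS only if ACLS began at the moment of arrest.

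The age-85 point has no practical bearing on this cohort. The entry limit was 65 years, and only patients whose age was misjudged at the scene could exceed it.

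**Conclusion.** The point holds as an inconsistency within the model specification: the printed formula and the Table 2 rows define different models for direct-ACLS PEA/asystole, direct-ACLS VT/VF and sedated-but-moving patients. For an affected patient the size is exact: odds divided by 54.6, divided by 1.66, or multiplied by 2.16. The size for the study cannot be computed from the article. Any effect on AUC, calibration or sensitivity requires both that the formula is coded as printed and that such patients are among the 92. The example probabilities rest on assumed predictor values; the odds factors and the cut-off ranges do not. Because the rows and text make the intended model recoverable, this is a minor to moderate correction. It is still worth making before the probabilities are calculated, since the plan points to Table 2 without saying which part governs.

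**What to change.** Reprint the four category terms of the formula with their full conditions:

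- -0.505 if no direct ACLS and VT/VF;
- -4.000 if no direct ACLS and PEA/asystole;
- +0.772 if not moving or breathing and sedation or muscle relaxant given;
- +1.528 if moving or breathing.

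Add a sentence to the Statistical analysis section stating that the Table 2 categories govern the calculation. Before the blinded probabilities are locked, run the code on test cases of the three affected kinds and compare the results with hand calculation from the rows. As a separate small correction, state the constraint as age < 85.

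The cost is one corrected line, one added sentence and a short code check. The model, the endpoint and the planned analyses do not change.
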